**General data**												
First Name	x											
Last Name	x											
Sexe	x											
Date of birthday	x											
Phone number	x											
Adress	x											
Center	x											
Medical history and comorbidity	x											
Concomittant medication	x											
Preoperative chemotherapy	x											
History of liver surgery	x											
ASA score		x										
Date of 1st consultation	x											
Operating date					x							
Type of liver resection					x							

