### Randomization

Patients will be randomized in blocks, with a distribution of 1:1 for the control group and experimental group. The block size will be random and will be informed in the report of the study. Randomization will be stratified by investigator centre, type of hepatectomy and presence of an underlying hepatopathy.

The randomization list will be established using the software NQuery Advisor®v6.01, a validated system using a generator of pseudo-random numbers, so that the sequence of treatments is both repeatable and non-predictable. The physician-investigator will enter data for inclusion in computerized case report forms (eCRF), implemented using the software “Cleanweb” (Telemedicine technologies). The physician-investigator will be able then to access the randomization module of the software that will award the group in which the patient is randomized. A unique identification alphanumeric number will be assigned to each patient: “number of the center (3 characters) – Number of inclusion in the center (3 characters) - Initials of first and family names (1 and 1 characters) - randomization group”. Patients who left the study keep their number included if it has already been given. New patients will always receive a new issue of inclusion.

The randomization list will not be known in advance by the investigators. The statistical analysis and preparation of tables and graphs for the report of the study by the statistician of the study will be blinded to the extent possible. The unblinding may take place only after all data has been entered into the database of the study, all requests have been closed and the database has been frozen by the Data Manager of the study.

If necessary, unblinding may be performed according to validated procedures of the promoter. Access to randomization codes during the phase of blinding will be monitored and documented and the documentation will be kept in the “CTMS (Clinical Trial Management System)”.

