### Statistical methods

#### Sample size calculation

The hypothesis of this phase IV trial is that immunonutrition will reduce overall postoperative 30-day morbidity rate. The sample size calculation is based on the detection of significant difference in the primary end-point parameter of the trial. We assumed a postoperative complication rate of 36% in the conventional group (Arm B) according with several studies about complication rate after liver surgery. A reduction of 33.3% would be considered to indicate the efficacy of treatment. With an expected complication rate of 24% in the immunonutrition group (Arm A), the sample size necessary for the trial with a power of 80% and a one-sided significance level of 0.05 was calculated to be 180 patients per group. An assumed 10% drop-out rate in this trial (due to non-compliance, intolerance, etc.) will raise the sample size to 198 patients per group. Therefore, at least a total of 400 patients (200×2) have to be included to the trial.

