#### Statistical analyses

The statistical analysis will be based on the intention-to-treat principle with one-sided test for the primary and secondary endpoints. However, attempts will be made to analyse “per protocol”, “completer”, and “intent-to-treat” populations separately, when statistically appropriate. A p < 0.05 will be considered as significant.

First of all, an establishment of patient flow chart according with CONSORT 2010 statement [27] will be realized. This one will describe precisely the progress through the different phases of the randomized trial (enrolment, intervention, allocation, follow-up and data analysis).

Secondary, a description of demographic and clinic features of patients in the 2 groups will be calculated by using valid number, frequency count and percentage for categorical data and by using mean, standard deviation, 95%-confidence interval of the mean, minimum lower quartile, median and upper quartile for continuous data.

To study primary end-point (that is the rate of postoperative complication grading II, III, IV or V in Dindo-Clavien’s classification), Pearson Chi-square test or Fisher’s exact test will be used when appropriate.

To study secondary end-points, the Pearson Chi-square or Fisher’s exact test will be used to compare categorical variables between the 2 groups, and the independent-samples *t*-test will be used to compare continuous variables. A multivariate analysis will complete this statistical plan.

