### Ethical matters

This study is conducted according to the principles of the declaration of Helsinki and the principles of the Good Clinical Practices guidelines. This study was approved by ethics committee ‘Ile de France 1 (IDF1)’ of the Hotel-Dieu Hospital on May 2013 under the registration number 2013-A00481-44. Approval from the ‘Ile de France 1 (IDF1)’ ethics committee of the Hotel-Dieu Hospital is sufficient for the 6 study centers (Paul Brousse University Hospital, Saint Antoine University Hospital, Mondor University Hospital, Pitié-Salpetrière University Hospital, Kremlin-Bicêtre Hospital and the University Hospital in Lille).

The study has also been approved by the ANSM (Agence nationale de sécurité du medicament et des produits de santé) on May 2013.

This trial has been registered on Clinicaltrial.gov website under the identification number NCT02041871.

The institutional promoter is the Paul Brousse University Hospital, Villejuif, France. This study received a grant from the French National Cancer Institute (Institut National Cancer - INCa) in 2012 and the study protocol has undergone peer-review by the funding body.

The study products (ORAL IMPACT and IMPACT CONTROL) were donated by NESTLE Clinical Nutrition, France.

Informed consent will be obtained from each patient in a written form before enrolment and randomization.

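### The primary test ignores the three stratification factors: it is valid and keeps its planned power, but is conservative if those factors predict morbidity

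*Protocol article*

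**What the plan says.** The Randomization section of the protocol article states: "Randomization will be stratified by investigator centre, type of hepatectomy and presence of an underlying hepatopathy". The Abstract and the Protocol overview name the same three factors, and the overview defines hepatectomy type as major or minor. Ethical matters says that one ethics approval "is sufficient for the 6 study centers". That gives 6 × 2 × 2 = 24 strata, filled 1:1 in blocks of random size.

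Under Statistical analyses, the primary comparison is fixed as follows: "Pearson Chi-square test or Fisher’s exact test will be used when appropriate". The test is one-sided at 0.05 in the intention-to-treat population. No stratification or covariate is attached to it. The only reference to an adjusted analysis comes after the text on secondary endpoints: "A multivariate analysis will complete this statistical plan". It names no endpoint, model or covariates.

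The sample size section plans on these inputs: "We assumed a postoperative complication rate of 36% in the conventional group (Arm B"), "With an expected complication rate of 24% in the immunonutrition group (Arm A"), and "a power of 80% and a one-sided significance level of 0.05". It arrives at 180 per group, raised to 198 for drop-out and rounded to 400 in total.

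**The concern.** Blocked allocation within strata makes the two arms nearly equal in centre, hepatectomy type and liver disease. Differences in risk between strata then contribute almost nothing to the true sampling variation of the treatment difference. An unstratified chi-square test does not use this. Its variance is computed from the overall event rate and still contains the between-stratum spread. When the factors predict the outcome, the standard error is overstated and the test rejects too rarely, both under the null and under the alternative.

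At stake is some of the efficiency that stratification can provide, together with agreement between the design and its primary analysis. The article does not merely leave this open for an analysis plan to fill. It names the primary test, and that test does not reflect the randomization.

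**Working it through.** **1. The plan's own figure.** Inputs: 36% and 24%, one-sided 0.05 (z = 1.645), 80% power (z = 0.842), mean rate 0.30.

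n per group = [1.645 × √(2 × 0.30 × 0.70) + 0.842 × √(0.36 × 0.64 + 0.24 × 0.76)]² / 0.12²

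= [1.645 × √0.42 + 0.842 × √0.4128]² / 0.0144 = 179.3, rounded up to 180.

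This is the stated figure, so the trial was sized for an unstratified chi-square test. The power of that test is Φ[(0.12 × √n − 1.645 × √0.42) / √0.4128]. This gives 80.1% at 180 per group and 83.7% at 200.

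**2. Simulation.** Taken from the article: N = 400, 24 strata, 1:1 allocation, overall rates 36% and 24%, one-sided 0.05. Assumed, because the article does not give them: blocks of 4; centre shares of 30, 20, 15, 15, 10 and 10%; half of resections major; 30% with liver disease; and the prognostic strengths below. There were 20,000 trials per scenario, so the Monte Carlo standard error is about 0.0015 for size (√(0.05 × 0.95 / 20,000)) and about 0.25 points for power (√(0.85 × 0.15 / 20,000)). CMH is the Cochran-Mantel-Haenszel test over the randomization strata. The SD of centre effects is on the log-odds scale.

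| Assumed strength (OR major; OR liver disease; centre SD) | Size, Pearson | Size, CMH | Power, Pearson | Power, CMH | Power given up (points) |
|---|---|---|---|---|---|
| None | 0.050 | 0.049 | 84.1% | 83.8% | −0.3 |
| Weak (1.5; 1.25; 0.2) | 0.047 | 0.048 | 84.3% | 84.4% | 0.1 |
| Moderate (2; 1.5; 0.3) | 0.046 | 0.051 | 84.4% | 85.3% | 0.9 |
| Moderate to strong (2.5; 2; 0.4) | 0.042 | 0.049 | 85.1% | 86.8% | 1.7 |
| Strong (3; 2.5; 0.5) | 0.038 | 0.049 | 85.3% | 88.0% | 2.7 |
| Very strong (4; 3; 0.7) | 0.032 | 0.050 | 86.6% | 90.5% | 3.9 |

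A repeat simulation of the same design gave power, Pearson against CMH, of 83.3/83.1% (none), 84.9/85.0% (weak), 85.1/86.1% (moderate) and 84.9/87.5% (strong). Pearson size fell from 0.050 to 0.040.

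**3. Analytic check of the size.** Under the null with a common rate of 0.36, the true variance is about r = 1 − SD² / (0.36 × 0.64) of what Pearson assumes, where SD is the spread of stratum risks. The true one-sided size is then about 1 − Φ(1.645 / √r).

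- Moderate: SD 0.116, r = 0.942, 1.645 / √r = 1.695, size 0.045 (simulated 0.046).
- Strong: SD 0.184, r = 0.853, 1.781, size 0.038 (simulated 0.038).
- Very strong: SD 0.225, r = 0.780, 1.862, size 0.031 (simulated 0.032).

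The formula and the simulation agree.

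**4. With 10% lost (N = 360).** Power, Pearson against CMH, is 80.8/81.6% at moderate and 82.0/85.0% at strong effects. The unstratified test still reaches 80%.

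**5. Sparse strata.** The average stratum holds 400 / 24 ≈ 17 patients. Under the assumed shares, the smallest (a 10% centre, major resection, liver disease) holds 0.10 × 0.5 × 0.3 × 400 = 6. CMH kept its size in the simulation even so.

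**The case against.** The best defence is that nothing in the plan fails. The named test does not inflate false positives, the sample size was computed for exactly this test, and the planned power is kept. The benefit of stratifying rests on prognostic strengths that the article does not give. With no or weak effects it is nil, and at moderate strength it is about one point. All of this stands, and it makes the point one of efficiency and consistency.

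Four stronger readings are tempting, but the article does not support them.

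- *The trial is underpowered or its error rate is wrong in the harmful direction.* The calculations show the opposite: power is at least 80% and the size is at or below nominal.
- *The Fisher option costs a further three points or so.* That is its arithmetic cost if it were used (81.2% against 84.1% with no prognostic effect). But Fisher is conventionally reserved for small expected counts, and at a 30% mean rate each arm of 200 expects about 60 events. Pearson would apply.
- *The primary confidence interval will be too wide.* The article specifies none for the primary comparison.
- *The analysis will stratify on the operation actually performed.* Table 3 records "Type of liver resection" on the operating day, but nowhere does the article say that this variable will enter a stratified analysis.

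The planned multivariate analysis may well adjust for these factors, and an article can leave its covariates to a fuller document. It is still an addition and does not replace the named primary test.

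**Conclusion.** The mismatch is real and stands in the article itself: randomization is stratified by three factors, and the primary test uses none of them. The consequence is modest. The unstratified test is valid and meets its power target, but it is conservative to the extent that the factors predict morbidity. The power given up is about 0 points (none or weak), 1 (moderate), 3 (strong) and 4 (very strong). The one-sided size falls from 0.05 to about 0.04 with strong effects and about 0.03 with very strong ones. The direction is certain whenever the factors are prognostic. The size rests on assumed odds ratios, centre spread and stratum shares, and its range starts at zero. With no prognostic effect, the stratified test was within 0.3 points of Pearson, so the change risks almost nothing.

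**What to change.** Name one primary test: a Cochran-Mantel-Haenszel test over the randomization strata, reported with the Mantel-Haenszel risk difference and its confidence interval. Define the strata by the values entered at randomization, and say so explicitly, because the operation performed is a post-randomization variable. Before unblinding, set a pooling rule for sparse strata, for example merging small centres. Keep the unstratified Pearson test as a sensitivity analysis.

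The article reports that data are still being collected and that unblinding follows database freeze, so the change can be made while the data are blinded. It costs a few sentences of analysis text, one extra programme and some care with small strata. It needs no additional patients, data or time.

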## Abstract

**Background:**

Malnutrition is an independent risk factor of postoperative morbidity and mortality and it’s observed in 20 to 50% of surgical patients. Preoperative interventions to optimize the nutritional status, reduce postoperative complications and enteral nutrition has proven to be superior to the parenteral one. Moreover, regardless of the nutritional status of the patient, surgery impairs the immunological response, thus increasing the risk of postoperative sepsis. Immunonutrition has been developed to improve the immunometabolic host response in perioperative period and it has been proven to reduce significantly postoperative infectious complications and length of hospital stay in patients undergoing elective gastrointestinal surgery for tumors. We hypothesize that a preoperative oral immunonutrition (ORAL IMPACT®) can reduce postoperative morbidity in liver resection for cancer.

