### Endpoints of trial

The primary endpoint of this trial will be the rate of overall complications classified in grade II-III-IV or V according to Dindo-Clavien classification [23] in the first 30 postoperative days (POD).

The secondary endpoints include: i)The rate of infectious complications classified in grade II, III, IV or V according to Dindo-Clavien classification in the first 30 PODs including: – Wound infection defined as any redness/ tenderness of surgical wound with discharge of pus– Abdominal abscess defined as deep collection of pus– Pulmonary tract infection characterized by abnormal chest X-ray with fever (>38°C) and WBC > 12.000 cells/mm^3^ and positive sputum or bronco-alveolar lavage.– Urinary tract infection defined as more than 10^7^ microorganisms per mL of urine– Bacteremia determined by two consecutive positive blood cultures without shock– Septic shock defined as positive blood cultures with circulatory insufficiencyii)The length of antibiotics treatment (in days)iii)The rate of non-infectious complications classified in grade II, III, IV or V according to Dindo-Clavien classification in the first 30 PODs including: – Postoperative biliary leak defined by the International Study Group of Liver Surgery (ISGLS) [24] as a bilirubin concentration in the drain fluid at least 3 times the serum bilirubin concentration on or after postoperative day 3 or as the need for radiologic or operative intervention resulting from biliary collection or bile peritonitis– Post-operative liver failure defined according the’ 50-50 criteria’ [25]: PT < 50% and total bilirubin >50 μmol/ml at POD 5.– Postoperative bleeding defined as the necessity of blood transfusion (*X*2 units) [26]– Respiratory failure characterized by the presence of dyspnea and respiratory rate >35/min or PaO2 < 70 mmHg– Circulatory insufficiency determined by unstable blood pressure requiring use of extra fluids and/or cardiac stimulants– Renal dysfunction defined by increase of serum urea and/or creatinine level (50% above baseline)– Renal failure defined as the necessity of hemodialysis– Multiple Organ Dysfunction Syndrome (MODS) characterized as a state of physiological derangement in which organ function is not capable of maintaining homeostasis– Wound dehiscence defined as any dehiscence of the fascia longer than 3 cmiv)The length of hospital and ICU stay (in days)v)Post-operative liver regeneration: all patients will undergo 4 successive volumetric helical computed tomography estimations of their liver volumes before surgery (day 0) then at POD2 (day 16), POD10 (day 24) and POD30 (day 44). Preoperative measurement of the future remnant liver will be performed using as landmarks hepatic vascular structures, identified by bolus injection of contrast, and the gallbladder. Post-operative measurements will be performed for the whole remnant liver and could be realized without injection of contrast. A volumetric assessment at POD 2 has been considered necessary to clearly estimate the volume of remnant liver. Liver regeneration at POD 10 (LR10) and 30 (LR30) are calculated by using the following formula, after assuming that the density of liver was close to 1:

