**Preoperative protein-energy malnutrition**												
Height	x											
Actual weight	x			x							x	x
BMI	x			x							x	x
Usual weight	x											
% of loss of weight in one and 6 months	x											
Albumin, prealbumin		x		x								
MNA-SF (for patients > 70 years old)	x											
Sarcopenia (Psoas area on CT scan)		x					x				x	x

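### The primary test is valid but makes no use of baseline nutritional status, which the protocol calls prognostic and records before treatment; adjusting for it would add a little power and robustness at almost no cost

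*Protocol article*

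**What the plan says.** The primary endpoint (Endpoints of trial) is binary: "the rate of overall complications classified in grade II-III-IV or V according to Dindo-Clavien classification", counted over the first 30 postoperative days. For it, Statistical analyses states that "Pearson Chi-square test or Fisher’s exact test will be used when appropriate". No covariate or stratum is attached to that test. The section ends by announcing a multivariate analysis, without naming its endpoint, model or covariates and without calling it primary.

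The Abstract's Background opens with "Malnutrition is an independent risk factor of postoperative morbidity and mortality" and puts the frequency at 20 to 50% of surgical patients. The Discussion repeats that malnutrition raises postoperative morbidity.

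Table 3 schedules these measurements before treatment:
- at the first consultation: weight, BMI and the percentage "of loss of weight in one and 6 months";
- at D0: albumin, prealbumin, psoas area and ASA score.

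The MNA-SF is collected only in patients over 70.

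On design, "Randomization will be stratified by investigator centre, type of hepatectomy and presence of an underlying hepatopathy". Nutritional status is not among the factors.

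**The concern.** A baseline variable that the protocol itself regards as prognostic for the primary outcome is balanced only by chance and is ignored by the deciding test. Two things follow.

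First, the part of the outcome variation that baseline nutrition explains stays in the standard error, so some power is lost in a trial planned at only 80%.

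Second, if the arms happen to differ in nutritional status, the unadjusted difference moves with that imbalance. In a nutrition trial such an imbalance would draw attention. An adjusted analysis whose covariates are chosen only after the imbalance is seen would be open to the charge of selection, and the unspecified multivariate analysis does not guard against this.

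**Working it through.** **Inputs from the protocol (Sample size calculation):** 36% complications in Arm B, 24% in Arm A, one-sided 0.05, 80% power, 180 per group. **Prevalence:** 20 to 50% (Abstract, for surgical patients in general). **Assumed:** the strength of the malnutrition–complication association, because the protocol gives none. Within-arm odds ratios (OR) of 1.5, 2 and 3 are used, with 4 as a stress case.

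**1. The plan's own figure.** Pooled two-proportion formula, no continuity correction:

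n = [1.645·√(2·0.30·0.70) + 0.842·√(0.36·0.64 + 0.24·0.76)]² / 0.12² = (1.066 + 0.541)² / 0.0144 ≈ 179.3, so 180 per group.

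This matches the stated 180 exactly. Unadjusted power at 180 is 80.1%.

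**2. Gain from adjustment.** Malnutrition is taken as a yes/no covariate with prevalence q, and the overall risks are held at 36% and 24%. Per patient in each arm:
- Unadjusted variance: 0.36·0.64 + 0.24·0.76 = 0.4128.
- Adjusted (standardised) variance: the sum over arms of (1−q)p₀(1−p₀) + q·p₁(1−p₁), plus q(1−q)(difference between the two stratum risk differences)²/2.

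Example, q = 35% and OR 3. The risks (not malnourished / malnourished) are 27.0% / 52.6% in Arm B and 16.7% / 37.6% in Arm A.
- Within-stratum variance: 0.2154 + 0.1725 = 0.3879.
- Last term: 0.2275 × 0.047² / 2 ≈ 0.0003.
- Relative efficiency: 0.4128 / 0.3882 ≈ 1.063.
- Effective size: 180 × 1.063 ≈ 191 per arm, giving 82.2% power.

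**3. Effect of a chance imbalance.** The SD of the between-arm difference in prevalence is √(2q(1−q)/180): 4.2, 5.0 and 5.3 points at q = 20, 35 and 50%. A difference of 1.96 SD is therefore 8.3, 9.9 or 10.3 points. The shift in the unadjusted difference is that imbalance times the average risk difference between malnourished and other patients. In the example: 9.85 × (25.6 + 20.9)/2 % ≈ 2.3 points.

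**4. Results at 180 per arm, over q = 20 to 50%:**

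| Assumed OR | Adjusted power | Gain over 80.1% (points) | n per arm for the same power | Shift at 1.96 SD imbalance (points) |
|---|---|---|---|---|
| 1.5 | 80.4% | 0.2–0.3 | 179 | 0.7–0.9 |
| 2 | 80.8–81.0% | 0.6–0.9 | 176–177 | 1.3–1.5 |
| 3 | 81.8–82.2% | 1.6–2.1 | 170–172 | 2.0–2.3 |
| 4 (stress case) | 82.8–83.5% | 2.6–3.3 | 164–167 | 2.6–2.9 |

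For OR 1.5 to 3, the shift is 0.7/12 = 6% to 2.3/12 = 19% of the target difference. The standard error of the difference is √(0.4128/180) = 4.8 points, so the shift is about 0.15 to 0.48 standard errors.

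**5. Simulation check** (40,000 trials per setting, unadjusted chi-square against a Cochran–Mantel–Haenszel test stratified by malnutrition). At q = 35% and OR 3, power is 80.7% unadjusted and 82.7% stratified. Across all settings the type I error of both tests is 4.8 to 5.2%.

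**The case against.** The strongest reply is that nothing here is wrong. A Pearson test on a randomised binary outcome is valid, and it matches the formula behind the sample size. Variation from chance imbalance is already inside its standard error, and an imbalance beyond 1.96 SD occurs in only about 5% of trials. All of that stands. It limits the point to efficiency and robustness.

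A second reply is that covariates belong in an analysis plan that is not shown, and that a multivariate analysis is already promised. This carries less weight. The article does not leave the primary test open; it names it. The multivariate analysis is unspecified and does not decide the trial.

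A third is that the protocol cites benefit regardless of baseline nutritional status. That concerns whether the treatment effect varies with nutrition. Adjustment needs only that nutrition predicts outcome, which the protocol asserts.

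A fair limit also stands: the calculation uses a yes/no malnutrition variable that the protocol does not define, so the gain from the actual measurements may differ.

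Some stronger readings are tempting but unsupported:
- A reader might infer that the primary result would be biased or its error rate inflated. Neither is so.
- A reader might take 20 to 50% as the prevalence in this trial. The figure is for surgical patients in general. None is given for non-cirrhotic liver resection, and patients unable to take oral nutrition are excluded.
- A reader might expect a much larger gain once albumin and ASA score are added. The protocol says nothing about how strongly these predict complications here, so no such gain can be claimed.

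**Conclusion.** The point holds as a worthwhile improvement, not as an error. The deciding test ignores a factor that the protocol calls prognostic and measures before treatment. With assumed odds ratios of 1.5 to 3 and prevalence of 20 to 50%, the cost is about 0.2 to 2.1 points of power at 180 per arm. An imbalance of about two SDs would move the estimate by 0.7 to 2.3 points. At an odds ratio of 2 or below the gain is under one power point, and it passes two points only for a strong association. The odds ratios are assumptions, and the prevalence is borrowed from a wider population. The change is still advisable because the data are already scheduled and planned power has little margin.

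**What to change.** Before unblinding, make the primary intention-to-treat analysis a logistic regression of the 30-day complication endpoint on:
- arm;
- the randomisation factors: centre, major or minor hepatectomy, and underlying hepatopathy;
- a short prespecified list of pre-treatment values already collected, for example 6-month weight loss, BMI, D0 albumin and ASA score.

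Report the standardised (marginal) risk difference with its test at the planned level, so that the quantity estimated remains the difference in rates on which the trial was sized. Use first-consultation or D0 values only. The D13 weight, albumin and other laboratory values are taken on the day before surgery, after the supplement has begun, and must not be covariates. State a simple rule for missing baseline values. Keep the Pearson test as a sensitivity analysis.

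The model is affordable. Six centres (5 terms), two further randomisation factors (2), four covariates with one term each (4) and arm (1) make 12 terms. At an average rate of 30%, 400 patients give about 120 events, or 10 per term.

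The cost is a paragraph of analysis wording, slightly more analysis work and a few missing baseline values to handle. No new data are needed. Study status says data are still being collected, and Randomization ties unblinding to the database freeze, so at the time of the article the change could still be prespecified cleanly.
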